3.4 Blinding level

In this open label study, participants, investigators and outcome assessors will not remain blinded to the treatment.

**4. Research subjects**

4.1 Diagnostic criteria

Diagnosis of oral candidiasis was established based on clinical manifestation and laboratory testing (smear test and/or fungi culture)

4.2 Inclusion criteria

1) age range of 18-70 years; 2) diagnosis of oral candidiasis was established based on clinical manifestation and laboratory testing (smear test and/or fungi culture); 3) patients with positive smear test are eligible for instant enrollment; 4) positive rate of fungi culture>80%; 5) negative reaction to pregnancy test in women and willing to take effective method of birth control in the period of trial; 6) voluntarily participating and Informed Consent Form being signed.

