5.2 Secondary outcome measurements

• Clinical improvement rate: (score of symptom and clinical sign at baseline- score of symptom and clinical sign post treatment)/ score of symptom and clinical sign at baseline

• Mycological: Eradication of organism (negative culture and negative microscopy)*

• Safety: Number of patient withdrawals due to adverse reactions; Incidence of adverse reactions (reported as side-effects).

*Candida albicans is found routinely in asymptomatic population, therefore, it would have been inappropriate to use mycological eradication as the primary outcome measure for the study.

The cure is defined as complete clinical response and eradication of Candida spp. at Day 7 or Day 14. A complete clinical response was defined as the complete disappearance of oral candidiasis lesions, and a partial clinical response was defined as ≥60% of clinical improvement rate compared with the score at baseline. <60% of clinical improvement rate and candida persistence, re-infection or species shifts were considered failures. Finally, biologic, local, and general safety was compared between treatments.

Participants will also be required to complete their daily diaries from the start of the treatment period until the end of the treatment period. Blood tests for full blood count and liver and kidney function tests will be conducted at initial assessment and during the final clinic visit (week 4).

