8.3 Research process

Potential participants will undergo preliminary screening for eligibility during visit 1 by investigators, which will include a registered oral medicine specialist. Eligible participants will then undergo initial assessments for review of system (ROS), baseline data collection, which include the symptom scoring, grade of clinical sign of oral candidiasis, measurement of vital signs (temperature, blood pressure and heart rate. ECG), full blood count, kidney function test and liver function test. The candida-related laboratory testing (smear test and fungi culture) will be performed to gather the baseline data of candida infection and colony forming unit count. A daily diary will then be given to record the change of symptoms and occurrence of adverse events and use of topical treatments during the 2-week treatment period. After signing the consent form, participants will be randomly assigned to either the treatment (miconazole mucoadhesive tablet) group or the control (itroconazole capsule) group and the treatment period will start. During this clinic visits, participants will be given 1 weeks’ worth of miconazole mucoadhesive tablet or itroconazole capsules and daily diaries for the fortnight.

In visit 2 of 1week after, the participants will be re-evaluated on the symptom scoring, grade of clinical sign, vital signs, smear test and fungi culture). The participants will repeat 1-week treatment and record the daily diary during the following week. In visit 3 (the following day after the 2-week treatment period) and visit 4 (2-week follow up after treatment ceasing), the participant will be evaluated by performing clinical and laboratory examination as baseline.

Throughout the treatment period, other medication or therapies, such as anti-hypertension drugs, is allowed to be used on an ‘as needed’ basis. During this treatment period, participants will also be required to record their medication intake, including trial interventions, other medications intake and occurrence of adverse events to assist with compliance monitoring and acceptability of intervention. Participants will be asked to return their medication pack to enable the counting of left-overs as well as part of participant adherence monitoring.

[figure not shown]

Figure 2. Outline of trial protocol

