**11. Statistical Analysis**

11.1 Analysis set

Full analysis set (FAS): it refers to the data set of all subjects participating in

randomization and being evaluated after medication at least once. For those subjects who fail to observe all healing effect evaluation, we conduct the data transfer according to LOCF (last observation carry forward) principle.

Per protocol set (PPS): it refers to the data set of all subjects meeting inclusion criteria, inconsistent with exclusion criteria and completing therapeutic scheme. Analysis (per protocol, PP) is taken on data of all cases consistent with research scheme, with good dependency and completion of filling in contents specified by CRF.

Safety set (SS): It refers to the data set of subjects who are grouped at random, take the research drug and at least have one safety assessment after the baseline.

Baseline comparative analysis and curative effect analysis are conducted based on

FAS and PPS, and safety evaluation is conducted according to SS.

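### Inclusion criterion 4 is a group-level culture rate that no patient can meet or fail, so per-protocol membership is undefined; separately, eradication is scored without requiring a positive baseline culture

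*Protocol*

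**What the plan says.** Section 4.2 numbers six inclusion criteria. Item 4 is "positive rate of fungi culture>80" per cent. The text does not say of whom the rate is taken, whether it applies by centre or overall, or what follows if it is missed. The inclusion list in the protocol's abstract does not contain it.

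The laboratory basis for entry is set elsewhere. Section 4.1 and item 2 of section 4.2 rest the diagnosis on "clinical manifestation and laboratory testing (smear test and/or fungi culture"), and item 3 adds that "patients with positive smear test are eligible for instant enrollment". Section 8.3 has both tests done at baseline, before it describes randomisation: "The candida-related laboratory testing (smear test and fungi culture) will be performed to gather the baseline data of candida infection".

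The mycological outcome in section 5.2 is "Eradication of organism (negative culture and negative microscopy"). It has no condition on the baseline culture. The same section makes eradication part of cure: "The cure is defined as complete clinical response and eradication of Candida spp. at Day 7 or Day 14". It also counts persistence, re-infection and species shifts as failures. Section 5 places the candida elimination rate among the primary measures, whereas 5.2 places eradication among the secondary ones.

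On the per-protocol set (PPS), section 11.1 says "it refers to the data set of all subjects meeting inclusion criteria". The full analysis set (FAS) has no such condition; it needs randomisation and one evaluation after medication. On masking, section 3.4 says that "outcome assessors will not remain blinded to the treatment". Section 11.2 states a non-inferiority approach.

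**The concern.** There are two separate problems.

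**An eligibility rule that cannot be operated.** Efficacy is to be analysed on both the FAS and the PPS. If one inclusion criterion cannot be checked for a patient, two competent analysts can build two different per-protocol sets from the same data. In a non-inferiority trial the per-protocol result carries real weight, so its membership should follow from the protocol without judgement.

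**An outcome that is partly met at entry.** A patient with a positive smear and a negative baseline culture may be randomised. For that patient the culture component of eradication is already satisfied, and with no baseline isolate there is nothing from which a species could shift. If such patients show less treatment difference than the others, they pull the two arms together, and in a non-inferiority comparison that favours the claim.

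The second problem reaches beyond a secondary endpoint, because eradication is a component of cure and candida elimination also appears among the primary measures in section 5.

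**Working it through.** **1. Apply the entry rules to one patient.** Take a patient with lesions, a positive smear and a negative culture.

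- Item 2 (smear and/or culture): met.
- Item 3 (positive smear): eligible at once.
- Item 4: no answer is possible. Read as requiring a positive culture, it excludes the patient and contradicts items 2 and 3. Read as a recruitment target, it says nothing about this patient.

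PPS membership differs between the two readings. If the target is met, fewer than 0.20 × 380 = 76 randomised patients are culture-negative. On the planned 158 evaluable per arm, 0.80 × 158 = 126.4, so about 126 are culture-positive and up to about 32 per arm would be in the PPS on one reading and out on the other.

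**2. Reproduce the planned sample size.** Inputs from section 3.2: 85% efficacy, one-sided alpha 5%, power 80%. No margin is given. Assume 10 points and equal true rates:

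n = (1.645 + 0.842)² × 2 × 0.85 × 0.15 / 0.10² = 157.7, so 158 per arm.

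This matches the protocol's 158. Margins of 9 and 11 points give 195 and 131. Ten points is therefore a reasonable working assumption, but it remains an assumption.

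**3. Dilution, as an illustration.** Further assumptions: the 85% also serves as the eradication rate under itraconazole in culture-positive patients; the true rate under miconazole there is 75%, exactly at the margin; a fraction f of each arm is culture-negative and is eradicated at the same rate q in both arms.

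- Control rate: (1 − f) × 0.85 + f × q
- Test rate: (1 − f) × 0.75 + f × q
- Observed gap: (1 − f) × 10 points
- P(claim) = Φ[(0.10 − gap)/SE − 1.645], with 158 per arm

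For f = 0.20 and q = 0.85, the rates are 0.85 and 0.77. SE = √[(0.85 × 0.15 + 0.77 × 0.23)/158] = 0.0439, and P = Φ(0.02/0.0439 − 1.645) = 0.117.

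| Culture-negative | Observed gap | P(false claim), q from 85% to 100% |
|---|---|---|
| 0% | 10.0 points | 5.0% |
| 5% | 9.5 points | 6.3% |
| 10% | 9.0 points | 7.8–7.9% |
| 15% | 8.5 points | 9.6–9.9% |
| 20% | 8.0 points | 11.7–12.4% |

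If culture-negative patients show half the difference, the gap at f = 0.20 is 0.8 × 10 + 0.2 × 5 = 9 points, and the figure is about 7.8%. If they show the full 10 points, there is no dilution and it stays at 5%.

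**4. Cost of restricting to culture-positive patients.** With 85% in both arms and the same assumed margin, power = Φ(0.10/√(2 × 0.85 × 0.15/n) − 1.645). For n = 126 per arm this is Φ(2.223 − 1.645) = 71.8%. If all 380 were evaluable and 80% culture-positive, n = 152 and power is 78.7%.

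**The case against.** The strongest reply is that item 4 is a clumsily placed recruitment target, that the trial works without it, and that a mycological population is normally defined in the statistical analysis plan, which is not at hand. The last part has some force for the eradication analysis. It does not rescue item 4: eligibility and the PPS rule are protocol content, and no analysis plan can make a rate testable in one patient.

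Several stronger readings are tempting and are not supported:

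- *Item 4 lets culture-negative patients in.* It does not. They enter through the smear and/or culture wording and instant enrolment on a positive smear. Read as a target, item 4 would limit their number.
- *These patients cannot fail on eradication.* They can. They were admitted on a positive smear that must turn negative, and tests are repeated under section 8.3, so a later culture may be positive. Only the culture half is met at baseline.
- *Patients will be dropped after randomisation to hold the rate above 80%.* No section provides for this, and the FAS has no such condition.
- *Laboratory readers are declared unblinded.* Section 3.4 speaks of outcome assessors in general and never mentions those who read smears and cultures. Masking is also independent of item 4.
- *The false-claim rate is 12%.* That needs the full 20% culture-negative, no arm difference among them, and a margin that is not in the protocol.

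**Conclusion.** The point holds in two parts. First, item 4 is stated wrongly: it is a property of a group placed among patient criteria, and it leaves PPS membership of culture-negative patients undefined. This follows from the text alone and needs no assumption.

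Second, and independently of item 4, eradication and the eradication component of cure are scored in patients who may have had no positive baseline culture. This weakens the endpoint without emptying it. The size is unknown, because the protocol gives neither the culture-negative share nor the treatment effect in that group. Under the assumptions shown, the false non-inferiority rate on eradication runs from 5% (no dilution) to about 12% at the extreme. The latter is not an expected value.

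The missing statement on laboratory readers is a small, separate improvement and adds no weight to either part. The matter should be corrected, but it does not touch any stated sample-size input or the clinical-response outcome in the FAS.

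**What to change.** - **Section 4.2:** remove item 4 from the patient criteria, or restate it as a recruitment-monitoring target with an explicit note that it has no effect on PPS membership.
- **Section 11.1:** keep the FAS as defined for clinical response.
- **Section 5.2 and the analysis:** assess eradication, persistence, species shift and the eradication component of cure in patients with a positive culture from the pre-randomisation sample, whatever their later results. Report the same outcomes in the whole FAS as a sensitivity analysis. Baseline culture status comes from a sample taken before allocation, so this restriction does not select on post-randomisation events.
- **Section 3.4 (separate):** state that smear and culture readers receive specimens labelled by ID code only. Section 3.3 already assigns such codes.

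The cost is mainly wording, plus coded labels at nine hospitals. The real price is precision in the mycological analysis: if nearly 20% are culture-negative, about 126 of 158 per arm remain, with about 72% power under the assumed 10-point margin. The protocol should acknowledge this.

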4.3 Exclusion criteria

1) diagnosis of cryptococcosis or other systemic fungal infections; 2) a history of a known allergy or intolerance to miconazole nitrate and/or itroconazole; 3) use of rifampicin, rifabutin, isoniazid, phenobarbital, phenytoin, methylprednisolone, carbamazepine, terfenadine, astemizole or cisapride; 4) history of pregnancy or breast-feeding; 5) history of psychological disorder that enable to cooperate; 6) hepaticinsufficiency with serum aminotransferase and total bilirubin levels at 1.5 times the upper limit of normal, or active clinical signs 2 months prior to the trial; 7) serum creatinine levels at 1.5 times the upper limit of normal; 8) history of cardiac insufficiency such as ischemic heart failure; 9) history of hematological diseases; 10) use of systemic or topical antifungal therapy within 2 weeks before study entry ( patients received topical treatment with miconazole or nystatin cream or suppositor remain eligible for enrollment in the study); 11) diagnosis of chronic mucocutaneous candidiasis; 12) hyposalivation related disease or drug-taking; 13) HIV positive; 14) history of participating other clinical trials within 4 weeks before study entry.

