**Abstract of Research Scheme**

| Research topic | The Efficacy and Safety of Miconazole Nitrate 10mg Mucoadhesive Tablets Verus Itraconazole Capsules in the Treatment of Oral Candidiasis: A randomized, open label, multicenter phase III trial |
| --- | --- |
| Research objectives | To evaluate the Efficacy and Safety of Miconazole Nitrate 10mg Mucoadhesive Tablets in comparison with Itraconazole Capsules |
| Research design | A randomized, open label, multicenter phase III trial |
| Inclusion criteria | The inclusion criteria: 1) age range of 18-70 years; 2) diagnosis of oral candidiasis was established based on clinical manifestation and laboratory testing (smear test and/or fungi culture); 3) negative reaction to pregnancy test in women and willing to take effective method of birth control in the period of trial. |
| Exclusion criteria | The exclusion criteria: 1) systemic fungal infections or chronic mucocutaneous candidiasis; 2) a history of a known allergy or intolerance to miconazole nitrate and/or itraconazole; 3) use of rifampicin, rifabutin, isoniazid, phenobarbital, phenytoin, methylprednisolone, carbamazepine, terfenadine, astemizole or cisapride; 4) history of psychological or other disorder that unable to cooperate; 5) Abnormal liver and kidney function; 6) history of cardiac disorders such as ischemic heart failure; 7) history of hematological diseases; 8) use of systemic or topical antifungal therapy within 2 weeks before study entry; 9) hyposalivation related disease or drug-taking; 13) HIV infection; 14) history of participating other clinical trials within 4 weeks before study entry. |
| Index of efficacy | Primary: Evaluation of clinical symptoms (pain and burning sensation rating), signs (pseudomembrane and erythema grade).  Scondary: Mycological eradication of organism (by smear test and fungi culture) |
| Index of Safety | Bood pressure, electrocardiography, full blood count and liver and kidney function |
| Dosage regimen | Miconazole Nitrate 10mg Mucoadhesive Tablets Itraconazole 100mg Capsules |
| Course of treatment | 2 weeks treatment and 2 weeks follow-up |

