4.4 Recruitment

Patients will be recruited from nine dental hospitals from northern, southern, western and eastern China. The study will be staffed with a clinical research team, who will inform potential participants about the aims, methods and potential risks and benefits of this study. All the investigators from the nine centers will be trained prior to the initiation of the study. Participants will be informed that their participation is voluntary and that choosing not to participate or withdraw will not affect their care. Patients unable to understand or follow the study procedures will not be enrolled. Potential participants will be recruited to the study following signing the written informed consent including information about the trial.

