5.3 Safety monitoring

A blood sample will be obtained at baseline（day -3~0）, endpoint of 2-week treatment (day 14+1), 2-week follow-up visit （If the patient reported an abnormal blood result at 3rd visit, then additional blood test would be required in the 4th visit）. A full blood examination, assess liver and renal function. For the duration of the trial, the principal investigator will be contactable by telephone at all times. Any adverse medical events reported by the patient will be recorded in the patients’ medical records at each visit. All adverse events will be followed up from the date it is brought to the investigator’s attention until the adverse event has been resolved. In the occasion of a severe adverse event occurring after initiation of the trial, the event will be recorded and immediately reported to the SFDA, followed by a detailed written report. Participants will be identified by their ID codes to maintain confidentiality. Participants may be withdrawn from the trial by the investigator if a serious adverse event occurs.

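### As worded, the liver exclusion in section 4.3 needs aminotransferase and bilirubin both raised, so it admits a sign-free patient with a marked isolated aminotransferase rise

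*Protocol*

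**What the plan says.** **Eligibility.** Section 4.3, item 6, excludes "hepaticinsufficiency with serum aminotransferase and total bilirubin levels at 1.5 times the upper limit of normal". It adds one alternative, active clinical signs in the two months before the trial. Item 7 excludes "serum creatinine levels at 1.5 times the upper limit of normal". The Abstract of Research Scheme covers both organs in one line, "Abnormal liver and kidney function", with no threshold and no reference to section 4.3.

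**Liver tests after baseline.** Section 5.3 places the baseline sample at day -3 to 0 and the next at the "endpoint of 2-week treatment (day 14+1"). Section 8.3 lists no blood test at visit 2: "the participants will be re-evaluated on the symptom scoring, grade of clinical sign, vital signs, smear test and fungi culture". At visit 3, the day after the two-week course, and at visit 4, "the participant will be evaluated by performing clinical and laboratory examination as baseline". Section 5.2 instead names only the initial assessment and the final visit at week 4 for blood count, liver and kidney tests.

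**Use of the criteria.** "Patients will be recruited from nine dental hospitals" (section 4.4). The per-protocol set in section 11.1 is tied to the same criteria: "it refers to the data set of all subjects meeting inclusion criteria, inconsistent with exclusion criteria and completing therapeutic scheme".

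**The concern.** Item 6 is the operative liver safety criterion. It joins two laboratory markers with *and*, so on its plain wording a patient is excluded on laboratory grounds only if both reach the limit. An isolated aminotransferase rise, however large, does not meet it unless there were recent clinical signs.

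The protocol itself treats liver function as a safety index, and the control arm takes itraconazole 100 mg by mouth daily for two weeks. A patient admitted in this way would complete the course before the next planned liver test. The same uncertainty carries into the per-protocol set, because membership depends on whether the patient met an exclusion criterion.

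A smaller matter is that the abstract's line on liver and kidney function has no limit attached. Taken at face value, it does not describe the same population as items 6 and 7.

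**Working it through.** No figure in the plan needs reproducing, and no power or alpha calculation enters. The check compares the texts on example patients and counts the days between liver tests.

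**Assumptions.** *At 1.5 times* means at or above 1.5 x ULN; read exactly, it would exclude almost nobody on laboratory values. *Abnormal* in the abstract means above 1.0 x ULN. All example patients are free of clinical signs.

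**Step 1: example patients** (values in x ULN). *Both* takes *and* strictly. *Either* takes it loosely, as a list of tests any one of which is enough.

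| Aminotransferase / bilirubin / creatinine | 4.3, *both* | 4.3, *either* | Abstract, *both* organs | Abstract, *either* organ |
| --- | --- | --- | --- | --- |
| A: 4.0 / 1.0 / 1.0 | admits | excludes | admits | excludes |
| B: 1.2 / 1.0 / 1.0 | admits | admits | admits | excludes |
| C: 1.6 / 1.6 / 1.0 | excludes | excludes | admits | excludes |
| D: 1.0 / 1.0 / 1.2 | admits | admits | admits | excludes |
| E: 1.0 / 1.0 / 2.0 | excludes (item 7) | excludes (item 7) | admits | excludes |

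**Step 2: item 6 on its own.** Patient A is decided by the reading of one word. The two readings of item 6 differ for every sign-free patient with one marker at or above 1.5 x ULN and the other below it. On the literal reading there is no upper bound on the raised marker.

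**Step 3: abstract against section 4.3, with *and* read the same way in both.**

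- *Either* in both: A is excluded by both texts. B and D are excluded by the abstract and admitted by 4.3. The mismatch covers values above 1.0 and below 1.5 x ULN.
- *Both* in both: A is admitted by both texts. C and E are excluded by 4.3 and admitted by the abstract.

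So patient A does not separate the two texts on a consistent reading, but other patients do on either one. The texts agree throughout only if *abnormal* is shorthand for the limits in 4.3, which the protocol does not say.

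**Step 4: time without a planned liver test.**

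- Section 5.3, taking 14+1 as day 14 with a one-day window: shortest 14 - 0 = 14 days; longest 15 - (-3) = 18 days. Taking it as day 15 throughout gives 15 to 18 days.
- Section 5.2 alone, taking week 4 as day 28: 28 - 0 = 28 days to 28 - (-3) = 31 days.

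Sections 5.3 and 8.3 agree on a sample at visit 3, and 5.2 omits it. On every version, the next planned liver test comes when the course has ended.

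**The case against.** The strongest reply is that *and* in item 6 is loose drafting: it lists two tests, each with the same limit, and a clinician would exclude on either. The investigator also sees the baseline result, section 6.1 lets the researcher withdraw a subject, and section 5.3 provides for adverse event recording at each visit and telephone contact throughout. This is plausible and lowers the practical risk. It does not settle the text, since nothing in the protocol says that one marker is enough, and a safety criterion should not depend on each investigator supplying the intended word.

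A reader might infer more: that the abstract and section 4.3 contradict each other outright on the patient with an isolated rise, one excluding and the other admitting. The documents do not support that. The abstract also says *and*, joining liver with kidney, and does not say that any abnormality excludes. Patient A splits the texts only if *and* is read loosely in the abstract and strictly in item 6.

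Nor do the documents support the inference that hospitals would screen by different rules because some work from the abstract. The abstract is visibly condensed: it merges items, omits the breast-feeding exclusion and the exception for some topical treatments, and skips from number 9 to 13. Section 4.3 is the dedicated eligibility section, and section 4.4 has investigators at all nine centres trained before the start. What stands is the narrower mismatch in step 3, which depends on the assumed meaning of *abnormal*.

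The timing of liver tests is a separate design matter. It is used here only to show that no planned test during treatment would catch a patient whom item 6 let through. Likewise, the per-protocol question follows from the wording of the criteria and is not a second defect.

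**Conclusion.** The point holds for item 6. As worded, it admits a sign-free patient with a marked isolated aminotransferase rise to a trial with an oral itraconazole arm, and no liver test is planned until the two-week course is over. That conclusion rests on the literal reading of *and*. If either marker was meant to suffice, the rule is sound but misstated.

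The mismatch between the abstract and items 6 and 7 is secondary. It rests on taking *abnormal* as above the ULN.

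Severity is minor to moderate. The protocol gives no frequency of such results and no rate of hepatic harm, so neither a number of patients nor a risk can be put on it, and nothing here shows that a patient would be harmed.

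**What to change.** - Item 6: *aminotransferase or total bilirubin >= 1.5 x ULN, or active clinical signs within 2 months before the trial*.
- Item 7: *serum creatinine >= 1.5 x ULN*.
- Abstract: repeat these limits in place of the line without a threshold.

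The cost is a short wording amendment, which section 6 requires to go to the IRB for approval. No new test is needed, since liver and kidney function are already measured at baseline. Slightly fewer patients are eligible than under item 6 taken literally. Slightly more are eligible than under the abstract if that is read as excluding any liver or kidney value above the ULN, namely those between 1.0 and 1.5 x ULN. Membership of the per-protocol set on this criterion then follows from the recorded baseline values and clinical history, without interpretation.
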